## Methods

### Design

Prospective, randomised, two-arm, open-label, blinded-endpoint (PROBE) efficacy trial.

### Setting

Leicester (Leicester Diabetes Centre), UK; Montreal (Research Institute of the McGill University Health Centre-Centre for Outcomes Research and Evaluation, Canadian coordinating site), Canada; Edmonton (Alberta Diabetes Institute—University of Alberta), Canada.

### Trial time frame

We recruited the first participant on 24 September, 2021; we plan to complete recruitment by 30 June 2024 and interventions and final evaluations by 31 January, 2025.

### Eligibility criteria

Adults with T2DM 18–45 years of age who were diagnosed less than 6 years previously, are not on insulin therapy, and who have a HbA1c value between 6% and 10% if taking other glucose-lowering medication or between 6.5% and 10% if not taking any glucose-lowering medications. Eligibility criteria are detailed in table 2.

**Table 2 T2:** Inclusion and exclusion criteria

Inclusion criteria	
Age	18–45 years, inclusive
Type 2 diabetes	Physician diagnosis more than 3 months and less than 6 years previously
Haemoglobin A1c	6.5%–10%, inclusive if not taking glucose-lowering medication; 6%–10% if taking glucose-lowering medication
Body mass index	30 kg/m^2^* to 45 kg/m^2^, inclusive if White or Indigenous† 27 kg/m^2^* to 45 kg/m^2^, inclusive if other background, including mixed
Weight stability	Weight changes of less than 5 kg over the prior 6 months
Walking ability	Able to walk without assists and to participate in structured exercise training requiring the lower limbs
Capacity	Able to understand written and spoken English and/or French Able to provide informed consent
Willingness	Willing to be randomised and able to participate Willing to attend supervised exercise sessions, if so randomised Willing to adopt low energy diet, including abstinence from alcohol, if so randomised Willing to self-monitor glucose and blood pressure at the required frequency, if randomised to the low energy diet plus supervised exercise arm
Exclusion criteria	
Other diabetes types	Type 1 diabetes Gestational diabetes Monogenic diabetes
Poorly controlled blood pressure	Resting systolic blood pressure greater than 150 mm Hg or resting diastolic blood pressure greater than 90 mm Hg diastolic
Weight loss interventions	Currently participating in a weight reduction programme in addition to routine care. Previous bariatric surgery.
Medications	Insulin therapy* Use of licensed weight loss medications Significant changes in glucose lowering medications in the prior 3 months, as judged by study physicians Steroids by mouth or injection
Self-reported allergies to components of meal replacement products	Milk protein and/or other relevant allergies
Dietary practices	Dietary practices that prohibit the use of meal replacement products
Pregnancy and lactation	Pregnancy Lactation Planning to become pregnant in the next 8 months
Eating disorder	Self-reported or diagnosed
Substance abuse	Alcohol, drugs
Estimated glomerular filtration rate	Less than 60 mL/min per 1.73 m^2^
Retinopathy	Receiving or requiring active treatment for retinopathy
Clinically manifest vascular disease	Myocardial infarction Stroke Peripheral vascular disease
Other cardiac disease	Heart failure Atrial fibrillation Pacemaker Implantable cardioverter defibrillator
Other conditions that could impact weight and/or safety	Active malignancy or other chronic disease
Run-in phase	Failure to complete at least 5 or requested 7 days of accelerometer wear Failure to complete a food diary for 3 weekdays and 1 weekend day

*An exception is made for women who are on insulin therapy in case of pregnancy occurrence because of insulin’s established safety profile in pregnancy, rather than because of inability to control glycaemia on oral agents alone. If these women are willing and able to use a reliable form of contraception, they may be enrolled.

†Term for the original peoples of North America and their descendants; includes First Nations, Inuit and Métis peoples.

### Recruitment

Recruitment is primarily through clinics and family practices within the collaborative networks of participating centres and publicity through social media and other forms of media.

#### Run-in period

Candidates wear an accelerometer for seven consecutive days (wrist) and complete a 4-day food diary (three weekdays and one weekend day). Five days of accelerometer wear and the 4-day food diary are required to move beyond the run-in period.

### Measurements

In-person evaluations occur before randomisation, at intervention period midpoint (12 weeks±1 week; no MRI study at this time point), and at intervention period end (24 weeks±2 weeks) (figure 1, table 1).

**Figure 1 F1:**
[figure not shown]
Trial schematic. BMI, body mass index; HbA1c, haemoglobin A1c.

#### T2DM remission and related measures

The primary remission outcome requires a HbA1c below 6.5% at intervention period end, without glucose-lowering medication during the prior 12 weeks.^3–6^ Venous blood is sampled for HbA1c (high-performance liquid chromatography) measurement. Other related outcomes include HbA1c as a continuous variable, Homeostatic Model Assessment for Insulin Resistance and midpoint remission.

#### MRI-defined cardiac structure and function

Using the 3-Tesla platform^30^ (figure 2), we acquire cardiac cine images with retrospective electrocardiographic gating and an 18-channel phased-array cardiac receiver coil covering the left ventricle from base to apex (8 mm slice thickness, 2 mm gap with temporal resolution <50 ms and reconstructed to 30 phases). Using cmr42 software (CircleCardiovascular Imaging, Canada), we assess end-diastolic and end-systolic volumes, ejection fraction, myocardial mass, peak diastolic filling rate, systolic global longitudinal and circumferential strain, (simplified) long axis strain, and circumferential and longitudinal peak early diastolic strain rates (figure 3).

**Figure 2 F2:**
[figure not shown]
Core MRI protocol of the RESET for REMISSION trial. The core protocol can be completed in under 30 min and comprises: localisers, fat-water imaging (Dixon), which allow assessment of subcutaneous and visceral adiposity (optional PROFIT -1 which adjusts liver fat measurement for fibrosis); cardiac cine imaging comprises long axes and complete coverage of the left ventricle and perpendicular to the thoracic aorta allowing calculation of myocardial volumes, mass, ejection fraction, strain/strain rates (see figure 3) and aortic distensibility; finally native T1 mapping in a single midventricular slice will be acquired as a surrogate marker of myocardial fibrosis. PROFIT1, simultaneous proton density fat fraction imaging and water T1 -mapping with low B1+ sensitivity; SA, short -axis.

**Figure 3 F3:**
[figure not shown]
A typical example of strain analysis from cardiac MRI cine imaging. Top panelbmjopen-2022-063888: Two-chamber view which allows derivation of longitudinal strain/strain rate; bottom panel mid ventricular short axis from which circumferential strain and strain rate is derived. Left: images showing color representations of longitudinal and circumferential strain at end-diastole and end-systole, with green showing 0%, light blue showing—10% and dark blue showing—20% strain (more negative indicating higher strain). Middle: graphs showing global longitudinal strain and global circumferential strain. Right: graphs showing longitudinal and circumferential strain rate throughout the cardiac cycle. PEDSR, peak early diastolic strain rate, a sensitive measure of diastolic relaxation and a key secondary outcome.

We quantify aortic stiffness, at the pulmonary artery bifurcation with simultaneous blood pressure recording, using Java Image Manipulation (Xinapse Software, Essex, UK).^29^ We characterise myocardial tissue using a modified look-locker inversion-recovery sequence for a mid-level native T1 map. High native T1 time, and is a surrogate marker of diffuse interstitial fibrosis.

#### Adiposity and lean measurements

We measure weight (nearest 0.1 kg) and height, waist, hip and neck circumferences (nearest 0.1 cm) and use DXA (GE Lunar iDXA) for total fat and lean mass (table 1). We acquire MRI images for visceral, subcutaneous, hepatic and pancreatic adipose tissue using the chemical shift encoded (DIXON) approach. Taylor’s twin cycle hypothesis^31^ emphasises hepatic fat accumulation in T2DM development, leading to insulin resistance along with pancreatic fat accumulation that impairs beta-cell function.

#### Optional MRI sequences

Time permitting, optional sequences include simultaneous PROton Density Fat Fraction Imaging and Water T1-Mapping with Low B1+Sensitivity of the liver (fibrosis), thigh (skeletal muscle volume) and heart (intramyocardial fat).^32^ In Montreal, and time permitting at other sites, we perform oxygen sensitive CMR with hyperventilation and breath-holding, enabling ischaemia/microvascular dysfunction detection without contrast.^33^ In Leicester, participants receive manganese contrast infusion, with repeated T1 mapping every 2.5 min for 30 min, to assess calcium handling.^34^

#### Resting metabolic rate, fitness and strength

Following overnight fast, we conduct indirect calorimetry (ventilated hood system) for resting metabolic rate. We perform fixed speed treadmill exercise testing with increasing gradient (1% each minute) and a rolling average of 10 breaths for oxygen consumption and carbon dioxide production. The test continues to volitional exhaustion; 100% of age-predicted maximum heart rate (85% if using beta-blocker medication) plus respiratory exchange ratio ≥1.15; or ECG changes or symptoms of concern. We assess peak oxygen consumption, heart rate and blood pressure. The peak force output of handgrip is determined across three measures in each hand. We apply the Short Physical Performance Battery,^35^ WHO Disability Assessment Schedule 2.0 questionnaire^36^ and the Medical Research Council dyspnoea scale (MRC Dyspnoea Scale).^37^

#### Diet, physical activity and sleep

The 4-day food diary is repeated at intermediary and final evaluations for daily intakes (table 1). In addition to run-in, participants wear an accelerometer for the 7–14 days period proximate to the intermediary and final assessments. Accelerometer data is captured at 30 Hz (processed through the open source R program GGIR)^38^ for daily averages of steps, overall acceleration, and intensity gradient metric, and total time at sedentary, light and moderate to vigorous intensities. Overnight wear permits capture of sleep time, night duration and their ratio (sleep efficiency).

#### Cardiometabolic profile

We assess seated blood pressure (automated sphygmomanometer, averaged systolic and diastolic five sequential measures). We sample blood for lipid profiles, creatinine, electrolytes and liver function tests; and urine for the albumin to creatinine ratio. Among those without RAAS inhibition for albuminuria, we assess hypertension remission at intermediary and final assessments (blood pressure values of 130/80 mm Hg without use of antihypertensive agents during prior 12 weeks.)

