**Methods and analysis:**

This prospective, randomised, two-arm, open-label, blinded-endpoint efficacy trial is being conducted in Montreal, Edmonton and Leicester. We are enrolling 100 persons 18–45 years of age within 6 years’ T2DM diagnosis, not on insulin therapy, and with obesity. During the intensive phase (12 weeks), active intervention participants adopt an 800–900 kcal/day low energy diet combining meal replacement products with some food, and receive supervised exercise training (aerobic and resistance), three times weekly. The maintenance phase (12 weeks) focuses on sustaining any weight loss and exercise practices achieved during the intensive phase; products and exercise supervision are tapered but reinstituted, as applicable, with weight regain and/or exercise reduction. The control arm receives standard care. The primary outcome is T2DM remission, (haemoglobin A1c of less than 6.5% at 24 weeks, without use of glucose-lowering medications during maintenance). Analysis of remission will be by intention to treat with stratified Fisher’s exact test statistics.

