##### Physician review

The study physician meets with the intervention arm participant to discuss antihyperglycaemic and antihypertensive medication withdrawal,^47^ given immediate lowering of glucose values and blood pressure with the dietary intervention. Glucagon-like peptide 1 receptors are stopped 1 week prior to the low energy diet. All other antihyperglycaemic medications are stopped the day that the diet is started. Except for ACE inhibitors or angiotensin receptor blockers prescribed for albuminuria (ie, RAAS blockade), participants stop antihypertensive medications on the day that the diet is initiated.

At weeks 1 and 2 follow-up (virtual or in-person), the physician reviews participant-recorded glucose and blood pressure data. Participants perform capillary blood glucose testing daily before breakfast and, on 1 day prior to physician follow-up, a 7-point glucose profile (measures before and 2 hours after food or meal replacement consumption and at bedtime). Antihyperglycaemic medications are not considered for reintroduction unless fasting morning capillary glucose is frequently 10 mmol/L or higher. Using the home blood pressure monitor provided, participants measure seated blood pressure each morning, after a 5 min rest period (second of two sequential measures). Antihypertensive agents are not be reintroduced unless systolic blood pressure values are generally 165 mm Hg or higher, as in the DiRECT trial.^48^ RAAS blockade may be interrupted with symptomatic hypotension.

Participants who may become pregnant are required to use reliable contraception. This is discussed, with referral as needed.

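### Week 12 hypertension remission requires 12 drug-free weeks that intervention participants seen before day 84 cannot have, and the primary outcome's drug-free period is worded in two ways

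*Protocol article*

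**What the plan says.** **Hypertension remission.** The Cardiometabolic profile section states that, in participants without RAAS inhibition for albuminuria, "we assess hypertension remission at intermediary and final assessments", and defines the outcome as "blood pressure values of 130/80 mm Hg without use of antihypertensive agents during prior 12 weeks". Table 1 lists it among the key secondary outcomes at both weeks 12 and 24, and Statistical analyses plans to analyse it at both.

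**Visit windows.** The Measurements section places the evaluations after randomisation "at intervention period midpoint (12 weeks±1 week; no MRI study at this time point), and at intervention period end (24 weeks±2 weeks").

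**Drug withdrawal, intervention arm.** In the Physician review section for the first two weeks, apart from RAAS blockade given for albuminuria, "participants stop antihypertensive medications on the day that the diet is initiated". For glucose-lowering drugs, "Glucagon-like peptide 1 receptors are stopped 1 week prior to the low energy diet" and "All other antihyperglycaemic medications are stopped the day that the diet is started".

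**Primary outcome.** The abstract requires an HbA1c below 6.5% at 24 weeks "without use of glucose-lowering medications during maintenance". The section on T2DM remission and related measures requires it "without glucose-lowering medication during the prior 12 weeks", and Aims uses the same 12-week look-back. The article lists diabetes remission at week 12 as an outcome but gives it no drug-free period of its own.

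**The concern.** At week 12 the required drug-free time is as long as the nominal time since the drugs were stopped. Any visit in the early half of the permitted window therefore falls short. An intervention participant who took an antihypertensive until diet start, stopped it as planned and now has a low blood pressure would be counted as a failure because of the appointment date alone. Controls have no planned stop date, so this particular error arises in the intervention arm and pulls the comparison against the intervention. The threshold also has no direction: the text gives values of 130/80 without saying below, or at or below.

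The primary outcome has a related but separate problem. Its two wordings describe the same period only when the final visit falls at week 24, and the window allows two weeks either side. A participant with HbA1c below 6.5% could be in remission under one wording and not under the other. Statistical analyses expects that control-arm remissions could number fewer than 2, so it is worth removing the choice before data are seen, particularly in an open-label trial.

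**Working it through.** There is no planned figure to reproduce; the check is date arithmetic.

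**Inputs**
- Week 12 visit window: 12 weeks ± 1, so days 77 to 91 (Measurements).
- Week 24 visit window: 24 weeks ± 2, so weeks 22 to 26 (Measurements).
- Drug-free time for hypertension remission: 12 weeks = 84 days (Cardiometabolic profile).
- Antihypertensive stop: day 0 of the diet (Physician review).
- Maintenance: 12 weeks, nominally from week 12 (abstract).
- Assumption: visit days are counted from diet start. The article does not state the origin of the clock. If it is randomisation and the diet starts later, the shortfall below grows by that delay.

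**Week 12 hypertension remission**

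Drug-free days = visit day − stop day; the rule needs at least 84.

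| Visit day | Drug-free days | Shortfall |
|---|---|---|
| 77 | 77 | 7 |
| 80 | 80 | 4 |
| 83 | 83 | 1 |
| 84 | 84 | 0 (no slack) |
| 91 | 91 | none |

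Visits on days 77 to 83 fail automatically. That is 7 of the 15 permitted calendar days (7/15 = 47%), which is a share of days and not of participants.

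The final visit is free of this problem: the earliest one is on day 22 × 7 = 154, and its look-back starts on day 154 − 84 = 70, well after the drugs were stopped.

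**Week 12 diabetes remission, only if the 12-week rule is meant to apply**

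Drugs stopped on day 0 give the same table. The class stopped one week earlier gives 77 + 7 = 84 days at a week 11 visit and meets the rule. So does a participant on no glucose-lowering drug at baseline.

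**Primary outcome at week 24**

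Look-back start = visit week − 12, compared with maintenance starting at week 12.

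| Visit week | Look-back starts | Difference from week 12 |
|---|---|---|
| 22 | week 10 | −2 |
| 23 | week 11 | −1 |
| 24 | week 12 | 0 |
| 25 | week 13 | +1 |
| 26 | week 14 | +2 |

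- Drug use confined to weeks 10 to 12, visit at week 22: fails the 12-week look-back, passes the maintenance wording.
- Drug use confined to weeks 12 to 14, visit at week 26: passes the 12-week look-back, fails the maintenance wording.
- A drug restarted around then and continued to the visit fails both; no drug from week 10 onward passes both.

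**The case against.** The fair case against is that this is narrow. Participants not on an antihypertensive at diet start are unaffected, those on RAAS inhibition for albuminuria are already outside the outcome, and nothing says how many others are treated. The low energy diet continues to week 12 unless ideal weight comes first, and the maintenance plan is made by the end of that week, so there is no reason to expect visits to cluster early. On the primary outcome, maintenance is nominally the 12 weeks before week 24, Aims and Methods agree with each other, and only the abstract's short form differs. All of this stands and limits the size of the point. It does not remove the conflict, because the article itself applies the 12-week rule to the week 12 visit and itself permits that visit at week 11.

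A reader might infer more than the documents support:
- *That every early visit rules out week 12 remission.* It does so only for hypertension remission in intervention participants treated until diet start.
- *That week 12 diabetes remission is equally affected.* The 12-week rule is attached to the assessment at the end of the intervention, and midpoint remission is named without one. The statement that dichotomous secondary outcomes are handled as for the primary outcome concerns the method of analysis. The full protocol or analysis plan may define the midpoint outcome.
- *That about half of treated participants fail automatically.* This turns 7 of 15 days into a share of people by assuming evenly spread visits and a clock that starts with the diet. The article states neither.

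**Conclusion.** The point holds in a limited form. As written, the Cardiometabolic profile, Measurements and Physician review sections conflict: intervention participants treated until diet start and seen on days 77 to 83 cannot reach week 12 hypertension remission, by a margin of 1 to 7 days. The direction of the error is against the intervention. The number affected cannot be computed, because the documents give neither the number treated at baseline nor the distribution of visit dates. The day count assumes a clock starting at diet start.

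The primary outcome's two wordings diverge by at most two weeks on either side of week 12, and matter only for short-lived drug use at about weeks 10 to 14 in someone whose HbA1c is below 6.5%. Such use is possible, since reintroduction is allowed and the week 12 HbA1c may guide treatment, but its frequency is not given. A reader might infer that the primary result is materially distorted; no effect on the remission rate or on power can be shown from the documents.

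**What to change.** 1. **Week 12 hypertension remission.** Define the drug-free period as running from intervention start, or the corresponding date in controls, to the visit. State the direction of the 130/80 threshold. Participants in whom a drug was reintroduced still count as non-remitters; only the automatic failure from an early visit disappears. The required period then varies with the visit date, from 77 to 91 days.
2. **Week 12 diabetes remission.** If the 12-week rule is meant to apply, use the same anchor and say so.
3. **Primary outcome.** Reconcile the abstract with Aims and Methods to a single definition before analysis. The 12-week look-back from the HbA1c sample, already given in Aims and Methods, is one candidate: the required duration is constant, although its start moves with the visit. Anchoring at week 12 instead would accept 10 drug-free weeks at a week 22 visit (22 − 12), which does not agree with the 12 weeks stated there.

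The cost is rewording. Medication dates are already needed to derive these outcomes, and no treatment rule or visit schedule has to change.

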#### Demographic factors, mental well-being and quality of life

Participants complete questionnaires on sex and gender, date of birth, ethnicity, employment, income, education, and marital status; anxiety and depression (Hospital Anxiety and Depression scale^39^); diabetes-related distress (Diabetes Distress Scale^40^) and quality of life (EuroQuol group 5-Dimensional 5-Level^41^).

#### Intervention arm continuous blood glucose monitoring

To quantify the pattern of blood glucose responses to the intervention in detail, continuous glucose monitoring devices will be worn for 7 –14 days preintervention, at intervention onset, midintervention and at the end of intervention, with computation of average glucose level, glucose variability (SD and coefficient of variation) and time within, above and below range.

#### Data gathering for process evaluation

Through a qualitative descriptive approach, we will explore experiences of intervention arm participants.^42^ We will use maximum variation sampling^43^ to capture those who did and did not achieve remission and variations in age, sex, ethnicity and location. Our individual audiorecorded and transcribed in-depth interviews (online supplemental appendix 1) are informed by the normalisation process theory framework^44^ and Capability, Opportunity, Motivation-Behaviour.^45^ Sampling will continue until saturation of themes is achieved.^46^

